## Methods

### Study design

This is a multi-centre, prospective, post marketing surveillance study with a follow up period of 15 years (ClinicalTrials.gov Identifier: NCT00208455). It will be open, non-randomised and non-stratified. The primary objective is to evaluate the five-year survivorship of the new cementless short stem. The secondary objectives of this investigation are to evaluate the long-term survivorship and the clinical performance of the implant, the impact on the subjects health related Quality of Life and the affect of the prosthesis on bone mineral density.

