### Study population

The study will be conducted in four centres (UK, Italy, Spain and Germany). The recruitment target is 200 subjects, with each centre recruiting 50 subjects. The study has been approved by the ethics committees of Southmead LREC (Bristol, UK), Ospedale San Pietro (Rome, Italy), Hospital Arnau de Vilanova (Valencia, Spain) and University of Regensburg (Regensburg, Germany). Patients included will be aged between 18 and 70 years, suitable for a cementless primary THA and able to understand the study and co-operate with the study follow up visits. The main primary diagnosis will be osteoarthritis. However, other diagnoses will be included such as rheumatoid arthritis, avascular necrosis, developmental dysplasia of the hip or fractures. Excluded patients will be those with other conditions or disorders, unrelated to their hip replacement, that would affect their long-term involvement in the study and patients already participating in other research studies. Only one hip per patient is entered into the study. Patients undergoing a simultaneous bilateral or with a problematic or recent contralateral hip replacement will also be excluded.

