### Statistical analysis

The survivorship will be calculated using both revision and radiological loosening of the implant as end-points for the analysis. Kaplan-Meier survivorship curves will be calculated. Analysis will be performed to assess whether the patient or surgical characteristics have any affect on the primary endpoints. In addition, multivariate analysis using Cox's Proportional Hazards modeling will be undertaken in relation to the survival analysis.

The statistical analysis will be performed by a qualified Biostatistician ([name], DePuy International, Leeds, UK) using the statistical package SAS Version 8 (SAS Institute Inc., [name]) and Microsoft Access. All significance tests will be two-sided and carried out at a 5% significance level, 95% confidence intervals will be regarded as appropriate.

All eligible subjects admitted to the study that receive treatment, and have at least one usable post-treatment assessment, will be included in the statistical analysis where possible. Protocol violators will not be included in the statistical analysis. If applicable, the number of ineligible subjects that received treatment and the reasons for ineligibility will be summarised.

Missing values will be excluded from the analysis as they will be assumed to be missing completely at random and so no loss of information or bias will occur if they are not included in the analysis. If more than 20% of values are missing for a particular analysis variable, then this may significantly bias the results, hence further statistical investigation methods may be employed to try and investigate the effect of missing values.

Subjects who withdraw or are lost to follow-up will be included in the analysis up to the point of withdrawal or last known assessment.

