## Discussion

Re-evaluation of the femoral biomechanics by Fetto et al. has shown that the lateral femoral column can be effectively used to carry compressive loads [26,34,35]. Starting from that concept, Santori et al. developed and used a custom-made short stem with a well-defined lateral flare in 111 patients since 1995. Recent clinical and radiographic reviews confirmed the excellent results and positive bone remodelling of these implants [18,19,29]. An uncemented, anatomic, proximally fixed femoral short stem that follows the concept of proximal load transfer through a prominent lateral flare has therefore been developed by an international team of surgeons. Due to the specific shape of the stem an adapted insertion technique is required to avoid damage to the great trochanter and gluteus muscles. The broaching and final implant insertion is performed using a slight curved movement. Biomechanical in vitro tests performed by Westphal et al. with this implant show that adequate stability can be achieved with the selection of a small implant size and cancellous fixation of the stem when good bone quality is present [32,33]. Therefore, a sufficient amount of healthy cancellous bone around the implant should already be considered in the pre-operative templating. To reduce the risk of a varus movement through a higher lever arm, long and extra long femoral heads should not be used with high offset implants. The implant lends itself to minimal invasive surgery done with a Smith-Petersen or MicroHip^® ^approach, where conventional straight stems with a lateral shoulder may increase the risk of damaging the great trochanter and/or the abductor tendons [36,37]. However, one major concern in short hip stems is primary and torsional stability. Whiteside et al. have shown that preserving the femoral neck can effectively reduce micromotion and increase torsional stability [31].

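### The only stated analysis set for five-year survivorship is per-protocol, so failures in some implanted hips would not enter the Kaplan-Meier estimate

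*Protocol article*

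**What the plan says.** All from the protocol article.

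- **Objective and design (Study design).** "The primary objective is to evaluate the five-year survivorship of the new cementless short stem". The study is post-marketing surveillance, and "It will be open, non-randomised and non-stratified". No concurrent control group is described.
- **Size (Study population).** "The recruitment target is 200 subjects, with each centre recruiting 50 subjects".
- **Endpoint and estimator (Statistical analysis).** "The survivorship will be calculated using both revision and radiological loosening of the implant as end-points for the analysis", and "Kaplan-Meier survivorship curves will be calculated".
- **Who is analysed (Statistical analysis).** Subjects who are eligible, were treated and "have at least one usable post-treatment assessment, will be included in the statistical analysis where possible". Then: "Protocol violators will not be included in the statistical analysis". For treated patients found to be ineligible, the section promises only a count and the reasons.
- **Who is kept (Statistical analysis).** Patients who withdraw or are lost stay in the analysis until withdrawal or their last known assessment.

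**The concern.** The article names one analysis population and no other. It is a per-protocol set, and it carries the primary result. Survivorship in a surveillance study is normally read as the experience of stems that were put in. Here it would be the experience of stems put in eligible patients with no recorded violation.

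There is no comparator in which the same exclusions might partly cancel. An excluded hip that is revised or loosens drops out of both the event count and the number at risk. With few failures expected among about 200 hips, a handful of omitted events would visibly change the headline figure and its confidence limits.

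**Working it through.** **1. Does the rule reach the primary analysis?** The exclusions are written for the statistical analysis as a whole. The Kaplan-Meier sentence in the same section names no separate population. Read together, the exclusions apply to five-year survivorship.

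**2. Is each filter needed for a survival estimate?**
- Violators: a hip with a violation still has a surgery date and an event or censoring date. Kaplan-Meier can use it.
- Ineligible treated patients: the same holds. Leaving them out narrows the population from stems implanted to stems implanted in patients meeting the criteria.
- Usable assessment: an early revision is an event whether or not a visit took place. This filter probably removes few hips, because Radiographic evaluation schedules a post-operative film before the 3-month visit.

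The plan already handles incomplete follow-up by censoring withdrawn and lost patients. It gives no reason for treating the first two groups differently.

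**3. Size.** The only figure in the plan is the target, 4 × 50 = 200, which reproduces. No expected survivorship, event rate or exclusion rate is given, so the counts below are assumptions. They use crude proportions with complete follow-up.

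Let N hips have F failures, and let E excluded hips hold f of them. The reported failure proportion is (F − f)/(N − E), against F/N for all implanted stems. One failure among 200 is 1/200 = 0.5 percentage point.

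With N = 200, F = 8 and E = 10:

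| Failures among the 10 excluded | Reported failures | Against 8/200 = 4.0% |
|---|---|---|
| 0 | 8/190 = 4.2% | 0.2 point higher |
| 3 | 5/190 = 2.6% | 1.4 points lower |
| 5 | 3/190 = 1.6% | 2.4 points lower |

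**4. Direction.** The reported figure is too favourable only if f/E exceeds F/N. The break-even is f = E × F/N = 10 × 8/200 = 0.4. A single failure among the ten gives 7/190 = 3.7%, already below 4.0%; no failure gives the small shift the other way.

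**5. Effect on the confidence limit.** With F = 10, E = 10 and f = 4, survivorship in all implanted stems is 190/200 = 95.0% (exact 95% CI 91.0 to 97.6). In the restricted set it is 184/190 = 96.8% (93.3 to 98.8). The estimate rises by 1.8 points and the lower limit by 2.3.

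**6. Range.** With 6, 10 or 16 failures and 5, 10 or 20 exclusions, omitting 4 failures raises survivorship by about 1.3 to 2.0 points, and omitting 5 by about 1.9 to 2.5. If no excluded hip fails, survivorship falls by 0.1 to 0.9 point.

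**The case against.** The strongest reply is that little in the document shows the exclusions to be related to failure. Much of it stands.

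- **Bias certain to favour the device.** A reader might infer this, but the direction depends on the failure rate in excluded hips, which is unknown. The 3-of-10 example assumes 30% failing there against 2.6% in the rest, about 11-fold. The 5-of-10 example assumes 50% against 1.6%, about 32-fold. At a common 4% rate, ten excluded hips would hold about 0.4 failures and the estimate would hardly move.
- **Missed visits treated as violations.** Nothing in the text says so, and the rule keeping withdrawn and lost patients up to their last assessment points the other way.
- **Risky implant combinations removed as violations.** The Discussion advises that "long and extra long femoral heads should not be used with high offset implants". That is surgical advice; no passage makes departing from it a protocol violation.
- **Ineligibility as an after-surgery finding.** The criteria under Study population are mostly baseline facts. They may be discovered late, but excluding on them narrows the population and is not in itself selection on outcome.
- **Failures hidden altogether.** The Abstract says peri- and postoperative complications will be registered. The gap is in the survivorship curve, not necessarily in all reporting.
- **Violator and usable are undefined.** The article is condensed, and the definitions may sit in the full protocol or analysis plan, so their absence is not a finding. A definition could narrow the exclusion but would not undo it.

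What the reply does not meet is the rule itself: violators are left out, ineligible treated patients are only counted, and no all-implanted set is named.

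**Conclusion.** The point holds as a fault in the choice of primary analysis set. As written, five-year survivorship describes eligible hips without a recorded violation, and failures in other implanted hips are left out of the curve. That rests on the text alone.

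Size and direction cannot be determined from the document. Each omitted failure is worth about 0.5 percentage point. Under the assumed counts, the effect runs from a slight understatement of survivorship, when no excluded hip fails, to an overstatement of about 2.5 points, when five failures are omitted. The overstatement requires excluded hips to fail more often than the cohort as a whole, which is plausible but not shown. The usable-assessment filter contributes little.

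**What to change.** Replace the analysis-set wording for survivorship with, for example:

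*The primary survivorship analysis includes every enrolled hip in which the study stem was implanted, with time measured from the date of surgery, regardless of later findings on eligibility or protocol adherence. Revisions are counted whether or not a scheduled visit took place. Revision status is ascertained in the same way for all hips. Hips without an event are censored at the last date on which their status is known.*

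Two details matter. The set should be hips in which the stem was implanted, because including attempted implantations would change the question. Status must be sought equally for all hips; otherwise hips with no visits would contribute only when a failure happens to be reported, which would bias survivorship downwards.

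Keep the present eligible, violation-free set as a secondary per-protocol analysis.

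The cost is one paragraph of analysis wording and no new scheduled visits, with some effort to establish revision status where visits were missed. Reported survivorship may be slightly less favourable, and the primary set will include some patients outside the eligibility criteria.

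### The only stated analysis set for five-year stem survivorship leaves out implanted stems in protocol violators and ineligible subjects, so survivorship would be expected to be overstated if those stems fail more often

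*Protocol article*

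**What the plan says.** The Study design section of the protocol article describes the study as follows: "This is a multi-centre, prospective, post marketing surveillance study with a follow up period of 15 years". On allocation it adds: "It will be open, non-randomised and non-stratified". Its statement of the aim reads: "The primary objective is to evaluate the five-year survivorship of the new cementless short stem". The Statistical analysis section names the events: "The survivorship will be calculated using both revision and radiological loosening of the implant as end-points for the analysis".

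The same section then sets out who is analysed:

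- Where possible, the analysis takes in eligible subjects who were treated and have one or more usable assessments afterwards.
- Violators are left out altogether: "Protocol violators will not be included in the statistical analysis".
- Subjects found ineligible after receiving the stem get a summary only: "If applicable, the number of ineligible subjects that received treatment and the reasons for ineligibility will be summarised".
- Withdrawals and losses are handled differently: "Subjects who withdraw or are lost to follow-up will be included in the analysis up to the point of withdrawal or last known assessment".

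The exclusion of violators carries no qualifier; the phrase about inclusion where possible belongs to the sentence before it. The article names no set of all implanted stems and no analysis that brings the excluded subjects back.

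**The concern.** The quantity of interest is how long the implanted stem survives. A stem that is implanted and later revised has failed, whether or not the patient met the entry criteria or the protocol was followed. A per-protocol set estimates survivorship only in subjects who met the criteria and had no violation, which is a narrower question than a surveillance study of the device sets out to answer.

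With a single arm, there is no comparator in which a similar exclusion could offset the effect, so any difference in failure risk between excluded and retained subjects goes straight into the headline figure. Few failures are likely among 200 stems, so removing even a handful of subjects can move the estimate.

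The article itself gives reasons to expect a difference in risk. Its Surgical technique section calls for a modified insertion technique with this type of stem. Its Discussion ties stability to implant size and bone quality, and says that short stems do not suit every patient. Departures in technique or selection are therefore the cases in which more failures might be expected. They are also informative for the planned analysis of patient and surgical characteristics.

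**Working it through.** **The plan's own figure.** The Study population section states: "The recruitment target is 200 subjects, with each centre recruiting 50 subjects". With four centres, 4 x 50 = 200, which agrees. The article gives no expected survivorship, precision target or violation rate, so every rate below is an assumption. The calculations use simple proportions without censoring.

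**Effect on the estimate.** Let F be five-year failure over all implanted stems, v the share removed (violators plus ineligible implanted subjects), r the failure risk in removed relative to retained subjects, and f the failure in the retained set, which is what would be reported.

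F = (1 - v)f + v·r·f, so f = F / (1 - v + v·r). The overstatement of survivorship is F - f.

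With F = 5% (10 of 200), reported failure and, in brackets, the overstatement in percentage points are:

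| Share removed | r = 1 | r = 2 | r = 3 | r = 5 |
|---|---|---|---|---|
| 5% | 5.00% (0) | 4.76% (0.24) | 4.55% (0.45) | 4.17% (0.83) |
| 10% | 5.00% (0) | 4.55% (0.45) | 4.17% (0.83) | 3.57% (1.43) |
| 20% | 5.00% (0) | 4.17% (0.83) | 3.57% (1.43) | 2.78% (2.22) |

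For example, v = 10% and r = 3 give 5% / (0.90 + 0.30) = 4.17%. The extreme corner is 5% / (0.80 + 1.00) = 2.78%.

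The sign can reverse. With r = 0.5 and v = 10%, 5% / (0.90 + 0.05) = 5.26%, so survivorship is understated by 0.26 points.

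**In whole counts.** Suppose 20 of 200 subjects are removed, 9 of the 180 retained fail and 4 of the 20 removed fail (r = 20% / 5% = 4).

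- Retained set: 1 - 9/180 = 95.0% (Wilson 95% interval 90.8 to 97.3%).
- All implanted: 1 - 13/200 = 93.5% (89.2 to 96.2%).

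The difference is 1.5 points, and 4 of the 13 failures are absent from the primary result.

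**Precision at equal risk.** Removing a share v widens the interval by a factor of about 1/√(1 - v): 2.6% wider at v = 5%, 5.4% at 10% and 11.8% at 20%.

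**The case against.** The strongest reply is that the bias is neither certain nor shown to be large. It needs r above 1. Many entry criteria in the Study population section, such as the age limits, participation in other research or a simultaneous bilateral operation, give no evident reason to expect more stem failures. In absolute terms the shifts are small: with 10 failures in 200 the Wilson 95% interval for survivorship is about 91.0 to 97.3%, and even the extreme case above, 97.2%, falls inside it. This stands as a limit on size and certainty. It does not rescue the rule, because a confidence interval computed from the retained set does not allow for a systematic shift.

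It could also be said that a full protocol or analysis plan, not shown here, may define violators or add a further set. A missing definition is not held against the article. But the article states the exclusion outright; a definition elsewhere would change how many subjects are removed, not the fact that they are.

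A reader might infer four stronger points that the document does not support:

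- **That survivorship is certainly overstated.** At equal risk there is no bias, and at lower risk it reverses.
- **That the violator rule contradicts the withdrawal rule.** This would need missed visits or withdrawal to count as violations, which the article does not say. Withdrawals and losses have their own rule, and the natural reading is that they are not violators.
- **That violations are classified once the outcome is known.** The article does not say when or how they are classified, and many eligibility errors concern facts fixed before surgery.
- **That complications are distorted or go unreported.** The Abstract says complications will be registered, and nothing says that those in violators will be left out.

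**Conclusion.** The point holds as a badly fixed rule, not as a missing detail. The only stated analysis set for the primary objective is per-protocol, and it discards implanted stems together with their outcomes. Upward bias is the expected direction where exclusions reflect departures in technique or patient selection. Its size cannot be determined from the article: about 0.2 to 2.2 percentage points of five-year survivorship if overall failure is 5%, 5-20% of subjects are removed and they fail 2 to 5 times as often. If they fail equally often, the cost is lost precision alone.

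**What to change.** In the Statistical analysis section, replace the sentence that excludes protocol violators, and align the eligibility restriction before it, with text to this effect:

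*The primary survivorship analysis includes every subject in whom the study stem was implanted, regardless of protocol violations or eligibility errors. An analysis without protocol violators and ineligible subjects is a sensitivity analysis only. The outcomes of violators and of ineligible subjects who received the stem are reported, along with their numbers and the reasons.*

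The cost is a change of wording and one extra run, provided that these subjects stay in follow-up. The downside for the sponsor is that the reported survivorship may be slightly less favourable.

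### Deleting missing values is said to cost neither information nor bias; the first is false, the second rests on an unsupported assumption, and the 20% trigger does not repair it

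*Protocol article*

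**What the plan says.** All of the relevant text is in the protocol article, Methods, Statistical analysis.

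- The rule and the consequence drawn from it: missing values are left out because they are "assumed to be missing completely at random and so no loss of information or bias will occur".
- The threshold, in the next sentence: "If more than 20% of values are missing for a particular analysis variable, then this may significantly bias the results". In that case "further statistical investigation methods may be employed to try and investigate the effect of missing values". No method is named.
- Subjects who withdraw or are lost "will be included in the analysis up to the point of withdrawal or last known assessment".

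The article gives no reason for the assumption, no check of it and no expected rate of missing data. The rule is not limited to particular variables. It therefore covers the Harris and Oxford scores and bone density, which serve the secondary objectives, and the covariates of the Cox model.

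**The concern.** The rule makes two claims, and each fails in its own way.

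**Information.** Deleted values carry no weight, so precision falls whatever the reason they are missing. The claim of no loss is false even when its premise is granted.

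**Bias.** Absence of bias follows if values are missing completely at random. Follow-up lasts 15 years and patients may be up to 70 at entry, so some would be about 85 at the end. Patients who are unwell or dissatisfied with the hip may be the ones who miss visits. Missingness may then be related to poor outcome, and a mean over those who attend would read too well.

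The threshold does not rescue the rule. If values are missing completely at random, no percentage produces bias, so the warning above 20% contradicts the sentence before it. If they are not, bias can arise below 20%, where the plan does nothing. Above 20%, action is optional and unspecified.

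At stake are the credibility of the long-term score and bone-density results and the precision of the multivariable model.

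**Working it through.** **Inputs from the article.** "The recruitment target is 200 subjects, with each centre recruiting 50 subjects" (Study population): 4 × 50 = 200, which reproduces the only sample-size figure given. The trigger is more than 20% missing per variable. Follow-up is 15 years. All missing rates, score differences, covariate counts and hazards below are assumptions, because the article gives none.

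**1. Precision when values are missing completely at random.** With a fraction m missing, n = 200(1 − m), and interval width is multiplied by 1/√(1 − m).

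| m | n left | width multiplied by |
|---|---|---|
| 5% | 190 | 1/√0.95 = 1.026 |
| 10% | 180 | 1/√0.90 = 1.054 |
| 20% | 160 | 1/√0.80 = 1.118 |

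None of these rows exceeds the trigger, and all of them lose information.

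**2. Whether a percentage can stand in for the mechanism.** Suppose 20% of patients do poorly and score 20 points lower. Let a and b be the missing fractions among good and poor outcomes. The poor share among those observed is q_obs = 0.2(1 − b) / [0.8(1 − a) + 0.2(1 − b)], and the bias of the observed mean is 20 × (0.2 − q_obs).

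| a | b | overall missing | q_obs | bias (points) |
|---|---|---|---|---|
| 20% | 20% | 20% | 0.20 | 0 |
| 15% | 40% | 20% | 0.12/0.80 = 0.15 | +1.0 |
| 10% | 60% | 20% | 0.08/0.80 = 0.10 | +2.0 |
| 16% | 32% | 19.2% | 0.136/0.808 = 0.168 | +0.6 |

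The same 20% goes with a bias of 0, 1.0 or 2.0 points, and 19.2% still gives 0.6. The percentage does not identify the problem.

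**3. A simpler illustration for a late hip score.** Bias = fraction missing × difference between observed and missing patients. With 15% missing and a difference of 8 points: 0.15 × 8 = 1.2. With a range of 4 to 12 points: 0.15 × 4 = 0.6 to 0.15 × 12 = 1.8. The trigger is not reached.

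**4. Complete cases in the Cox model.** With k covariates each missing independently at rate m, 200(1 − m)^k hips remain.

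- m = 5%: 171 for k = 3 and 155 for k = 5.
- m = 10%: 146 for k = 3 and 118 for k = 5.

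No single variable passes 20% in any of these. If missing values cluster in the same patients, fewer hips are lost.

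**5. Bias in the hazard ratio.** A large simulation was run with 2,000,000 subjects, constant hazards of 1% and 2% a year, one binary covariate present in 40%, and 15 years of follow-up. The hazard ratio was estimated as a ratio of event rates. The true ratio is 2.

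| Missingness | hazard ratio |
|---|---|
| none | 2.01 |
| completely at random, 20% | 2.02 |
| depends on the covariate only (35% v 10%) | 2.01 |
| depends on the event only (40% v 15%) | 2.06 |
| depends on event and covariate jointly (50% v 15%; 18.6% overall) | 1.26 |

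Only the joint mechanism distorts the ratio materially. When missingness depends on the event alone, the ratio holds but the share of retained hips with an event falls from 18.7% to 14.0%.

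**The case against.** **Bias is not shown.** The article reports no missing rates and no mechanism. A reader might infer that deletion does bias the scores and the Cox model, but the document does not support that. If values are missing completely at random there is no bias. The score figures above come wholly from assumed inputs, and no decision threshold is attached to a score. This objection stands.

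**The Cox model is less exposed than the scores.** The patient and surgical characteristics in Perioperative measurements are recorded before or during surgery, so their absence would not ordinarily depend on later failure. The joint mechanism that gave 1.26 is hard to motivate for such data. A reader might also infer that a third of the hips would be lost: eight covariates at 5% give 1 − 0.95^8 = 34%. But the article states neither the number of covariates nor their missing rate, and few failures would argue against so large a model. This stands too. What remains is lost cases and precision.

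**The primary analysis is mostly protected.** Keeping withdrawn and lost subjects to their last assessment is ordinary censoring, so Kaplan-Meier follow-up is not simply deleted. It would be wrong to infer that five-year survivorship is undermined. The same paragraph supplies no later scores and no missing covariates.

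**Detail may sit in a fuller plan.** The choice of method may well. That does not excuse a rule and a claim that the article itself states.

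**Conclusion.** The concern holds as a wrong statement and a poorly fixed rule. It should be fixed, but it does not threaten the primary objective.

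- **Certain:** the claim of no lost information is false, by 2.6%, 5.4% or 11.8% in interval width at 5%, 10% or 20% missing of 200. The trigger contradicts the assumption that it follows, and it does not test the mechanism.
- **Plausible but not demonstrated:** over-favourable long-term scores, illustrated at 0.6 to 1.8 points on an assumed 15% missing and an assumed deficit of 4 to 12 points. Bone density is open to the same risk, with no size that can be given.
- **Limited:** in the Cox model the expected harm is fewer complete cases and wider intervals. Bias there would need missingness tied to both event and covariate.
- **Largely unaffected:** Kaplan-Meier survivorship, because of the censoring rule.

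**What to change.** 1. Delete the statement that no information is lost and no bias occurs, and delete the 20% trigger.
2. Analyse the repeated Harris and Oxford scores with a likelihood-based mixed model using all visits, which is valid under missing at random. Do the same for bone density where repeated measurements exist.
3. Define the target as scores in living patients with the unrevised stem, so that values after death or revision are not treated as missing. The mixed model alone does not settle this, because it implicitly extrapolates beyond those events. The definition has to be stated alongside it.
4. At each visit, tabulate hips as scored, revised, dead or missing.
5. Report one sensitivity analysis for outcome-related missingness, whatever the percentage missing.
6. Use multiple imputation for Cox covariates if the number of complete cases falls appreciably.

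The cost is revised wording and a small amount of programming. No new data are needed.

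### Lost and withdrawn hips are censored under a stated no-bias premise, with no committed check on whether loss hides failures before the five-year result

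*Protocol article*

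**What the plan says.** All references are to the protocol article.

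- Study design: "The primary objective is to evaluate the five-year survivorship of the new cementless short stem". Long-term survivorship is a secondary objective, within a "prospective, post marketing surveillance study with a follow up period of 15 years".
- Study population: "The recruitment target is 200 subjects, with each centre recruiting 50 subjects".
- Statistical analysis, end-points and estimator: "The survivorship will be calculated using both revision and radiological loosening of the implant as end-points for the analysis", and "Kaplan-Meier survivorship curves will be calculated".
- Statistical analysis, losses: "Subjects who withdraw or are lost to follow-up will be included in the analysis up to the point of withdrawal or last known assessment".
- Statistical analysis, missing values: they are left out on the assumption that they are missing completely at random, and the text concludes that neither information loss nor bias follows. If more than 20% of the values of an analysis variable are missing, the text accepts that bias may arise and allows, without requiring, some unnamed further investigation.
- Abstract (Methods) and Radiographic evaluation: the later visits are at 24, 60, 120 and 180 months.

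No expected failure, loss or death rate is given anywhere.

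**The concern.** Kaplan-Meier with censoring at last assessment is valid if, at any time, a patient who leaves has the same future failure risk as one who stays. That is doubtful for a hip stem. A patient with a painful or loosening hip may seek care elsewhere, and radiological loosening can be seen only in those who come for an x-ray. The article does not say that this will happen, but it is plausible, and the resulting bias would favour the implant.

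The article is not merely silent here. It states a premise (no bias) and fixes the only check in a form that need not be carried out and does not address censoring. The premise is also unsound on its own terms. Leaving values out always loses information. And if values really are missing completely at random, no percentage of missingness creates bias, so the 20% sentence undercuts the assumption before it.

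At stake is the primary five-year figure, and with it the comparison with conventional cementless components foreseen in the Background.

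**Working it through.** **Inputs from the article.** N = 200 (4 centres × 50 = 200, which agrees); primary time point 5 years; adjacent visits at 24 and 60 months. There is no survivorship figure to reproduce. Every rate below is an assumption.

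**1. Gap before the primary time point.** 60 − 24 = 36 months. A patient seen at 24 months and then lost may be censored there, with stem status unknown for the 36 months up to the primary time point.

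**2. Outer bound.** With f failures and L lost, Kaplan-Meier is approximated by 1 − f/(200 − L/2), which counts lost hips as at risk for half the period. The worst case is 1 − (f + L)/200.

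| f | L | Kaplan-Meier | All lost fail | Gap |
|---|---|---|---|---|
| 6 | 20 | 1 − 6/190 = 96.8% | 1 − 26/200 = 87.0% | 9.8 points |
| 4 | 10 | 1 − 4/195 = 97.9% | 1 − 14/200 = 93.0% | 4.9 points |

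The approximate 95% half-widths, 1.96 × √(S(1 − S)/200), are 2.4 and 2.0 points.

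**3. Intermediate cases.** Take constant hazards over 5 years: failure a = −ln(0.95)/5 while followed, loss b = −ln(1 − loss)/5, and failure hazard k·a after loss. True five-year failure is

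1 − { e^(−5(a+b)) + b·[e^(−5ka) − e^(−5(a+b))]/(a + b − ka) }.

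Kaplan-Meier would show 5.0% in every row.

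| Loss by 5 years | k = 2 | k = 3 | k = 5 | All lost fail |
|---|---|---|---|---|
| 10% | 5.2% | 5.5% | 5.9% | 1 − 0.95 × 0.90 = 14.5% |
| 20% | 5.5% | 6.0% | 6.9% | 1 − 0.95 × 0.80 = 24.0% |

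The shift is 0.2 to 1.9 points.

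**4. Sampling error for comparison.** 1.96 × √(0.95 × 0.05/200) = 0.030, or about 3.0 points.

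**5. The trigger.** Even if the 20% rule were read as covering losses, it requires more than 20%. A loss of exactly 20% (0.20 × 200 = 40 patients) would not set it off.

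**The case against.** **Censoring at last contact is standard, and sensitivity analyses are usually left to the full protocol or SAP.** This is right, and their absence from an article is not the finding. The finding is what the article does state: a no-bias premise and a check that is optional and aimed elsewhere.

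**The missing-values sentences may not govern censoring at all.** That is a fair reading. But then no check in the article reaches the censored hips, while Kaplan-Meier still needs loss to be uninformative.

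**Loss may be small, and revisions may be learned of between visits.** Entry is limited to patients able to co-operate with follow-up, and complications are to be registered. Both reduce the risk. Neither settles the status of a patient who has left, and neither reveals loosening without an x-ray.

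**The uncertainty from lost hips need not exceed sampling error.** A reader might infer from the 87.0% figure that it does. That holds only towards the all-lost-fail bound. In the intermediate cases the shift stays inside the 3.0-point half-width. This limits the point, though a confidence interval does not cover bias of any size.

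**Deaths.** A reader might also infer that deaths over 15 years will outnumber failures and distort the result. The article does not support this: it gives no rates and does not mention death. With assumed constant hazards, N = 200 and 15-year failure of 10%, 15-year mortality of 5% gives about 19.5 failures and 9.5 deaths, while mortality of 20% gives 18.0 and 38.0. The order depends wholly on the assumption. One minus Kaplan-Meier exceeds the cumulative incidence of failure by 0.02 to 0.5 points at five years (failure and death each 2-10%). At 15 years the excess is 0.3 to 2.1 points (failure 10%, death 5-40%). This overstates failure, so it does not flatter the implant, and it matters mainly for secondary results. Kaplan-Meier remains a proper estimate of implant survivorship.

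**Conclusion.** The point holds for loss to follow-up and withdrawal. The article treats loss as harmless, commits to no check of that, and has a visit gap that can leave stem status unknown for up to 36 months before the primary time point. If loss is related to failure, five-year survivorship is too favourable.

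Under the assumed rates, moderately informative loss turns an apparent 5% failure into about 5.2-6.9%. The outer bound is much wider: 87.0% against 96.8% with 6 failures and 20 lost. The true effect depends on the number lost and on how they differ, neither of which can be known from the article. This should be put right, but it does not invalidate the design or the choice of Kaplan-Meier. No conclusion about deaths outnumbering failures follows.

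**What to change.** 1. Remove the statement that leaving out missing values causes no loss of information or bias. State instead that censoring assumes uninformative loss and that this will be examined whatever the percentage lost.
2. Before censoring a non-attender, seek revision status by letter or telephone where consent allows. This cannot recover radiological loosening, so the two end-points should be reported with that difference in mind.
3. Beside the five-year Kaplan-Meier figure, and the later ones, report the number lost or withdrawn, a worst-case curve counting those hips as failures at last contact, and intermediate scenarios with a raised failure hazard after loss (for example 2, 3 and 5 times).
4. Keep Kaplan-Meier as the headline. Cumulative incidence with death as a competing event at 10 and 15 years is at most an optional secondary addition.

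A count of lost hips that would overturn the conclusion is not requested, because the article states no performance threshold against which to define it.

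The cost is some contact effort and a little programming. The downside is that a less favourable lower bound appears beside the headline figure. Sample size and visit schedule are unaffected.
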